### Combined motor control and isolated lumbar extension resistance training (MC + ILEX)

The degenerative changes seen in the muscles of patients with LBP can be caused by poor motor control, which can lead to repetitive mechanical stress on surrounding structures, increasing the risk of instability, joint overloading, and pain [20]. Therefore, this intervention will consist of exercises that directly target the deep lumbar muscles with an overall aim of restoring proper coordination, control and co-contraction of these muscles to support the spine at rest and during movement [32, 33]. The intervention will follow principles of motor control and will include a cognitive phase (e.g. activation of the deep spinal muscles) and will transition to an associative and autonomous phase (e.g. functional rehabilitation) [34, 35]. The intervention will also include the coordination and optimal control of global trunk muscles [36, 37].

#### Phase 1: cognitive phase

The initial phase starts with an assessment of muscle activation and breathing patterns. The motor control program will be guided by deficiencies found during the assessment. The primary focus of the intervention is on the correction of the muscle patterns such as increasing the activation of the deep trunk muscles (e.g., multifidus and transverse abdominus muscles) and decreasing the activity of the global muscles (Table 2) [33, 36, 37]. Activation of the deep trunk muscles will be completed in a variety of starting positions that will be progressed in complexity as the patient improves. Before progressing to stage two the patient must be able to meet the following criteria: complete 10 reps while holding for 10 s, achieving activation with minimal feedback or cues, and be able to maintain a normal breathing pattern throughout the exercises [38].

**Table 2 Tab2:** Sample cues and positions for early Multifidus and Transerse Abdominis activation

Multifidus Activation	
Positions	Prone or on hands and knees (some people are better in 1 to start)
	Fingers on either side of spinous process; evaluation of different spinal levels from T1/T2 to T5/S1
Cues	Try to swell muscle up into my fingers
	Think about tilting pelvis without actually doing it
	Imagine tensing a cable from your pelvis up through your spine
Ideal Response	Symmetrical contraction
	No global muscle activation
	Normal breathing
	Able to hold 10 x 10s
**Transverse Abdominis Activation**	
Positions	Start supine or crook-lying
	Find neutral pelvis
	Place fingers slightly medial and inferior to ASIS
Cues	Try to pull your belly button down to the table
	Try to move your fingers together (medially)
Ideal Response	Gradual increase in tension; 10–15% effort
	Symmetrical contraction
	No global muscle activation
	Normal breathing
	Able to hold 10 x 10s

Breathing will be assessed supine and in sitting for asymmetry, expansibility and for the use of accessory muscles (e.g., sternocleidomastoid and scalene). Correction of breathing patterns with a focus on diaphragmatic breathing will be incorporated into the exercises of both phases of the intervention.

#### Phase 2

Once the patient is able to adequately activate the deep trunk muscles with minimal compensation of the superficial muscles, while maintaining proper breathing, participants will progress to phase 2. This will include the addition of loads to the muscles first into static positions and eventually into dynamic positions [37]. During this phase, the exercise will progress towards functional activities while maintaining lumbar position and coordination of the deep trunk muscles. Exercise difficulty and progression will be achieved by moving the participant into a more challenging position (e.g., supine to sitting), increasing the load (movement of limbs), and introducing the need for dynamic stability (moving to unstable surface such as sitting on an exercise ball). The goal of this phase is to progress to automatic activation of deep trunk muscle with coordination of superficial muscles.

Participants in this group will also complete isolated lumbar extensor strength exercise (ILEX) in parallel to the motor control (MC) exercises. This training will be completed on the MedX machine (Fig. 2). Participants’ one repetition maximum (1RM) will have been recorded during the baseline testing (refer to section below about baseline extensor strength assessment). They will perform 2 sets of 15–20 repetitions of lumbar extension at 55% of their baseline 1RM at 24°. Progressions will occur once the patient is able to complete 15–20 repetitions. For each progression the load will be increased by 5% [39, 40]. The MedX lumbar extensor machine, shown in Fig. 2, allows for isolated testing and strengthening of the lumbar extensor muscles through full range of motion in the flexion-extension plane of movement. Pelvic stabilization and lower body restraints eliminate the activation of synergistic and compensatory muscles, such as the glutes and hamstrings, allowing for isolated lumbar extensor strengthening.

**Fig. 2 Fig2:**
[figure not shown]
Schematic illustration of the MedX Lumbar medical machine. Image reprinted with permission [41]

### Data collection

All outcomes (as described further) will be obtained at baseline, 6-week and 12-week for both intervention groups. The self-reported outcomes will also be assessed 24-week post-intervention. All self-reported questionnaires will be completed either in-person using paper forms or through the LORIS system using a URL link. Imaging outcomes (e.g., MRI and ultrasound) and lumbar extensor muscle assessments (e.g., strength) will be obtained at the PERFORM Centre, Concordia University. Demographic characteristics will be obtained via a self-reported questionnaire at baseline, after the randomization.

### Outcome measures

#### Primary outcome

##### Multifidus muscle morphology

Multifidus muscle size and fatty infiltration (e.g., from L1 to L5) will be examined using T2-weighted and IDEAL (lava-flex, 2-echo) sequences obtained using a 3-Tesla GE MRI machine. The cross-sectional area (CSA) of the muscle will be taken on axial T2-weighted slices from the cranial view of L1 and the caudal view of L5; single level and total left and right 3D volume will be calculated. The overall area of lean muscle mass will be assessed using a highly reliable thresholding technique [42, 43], and DIXON axial water and fat images will be used to assess percent-fat signal fraction at each spinal level [44]:
$$ \%\mathrm{FSF}=\left({\mathrm{Signal}}_{\mathrm{fat}}/\left[{\mathrm{Signal}}_{\mathrm{water}}+{\mathrm{Signal}}_{\mathrm{Fat}}\right]\times 100\right). $$

#### Secondary outcomes

##### Multifidus muscle function

Multifidus muscle thickness at rest and during submaximal contraction will be evaluated by examining the changes in the muscle during contralateral arm lifts. Muscle thickness will be assessed using the Logic E GE ultrasound machine with a 5-MHz transducer. The submaximal and maximal contractions will be performed 3 times on each side in a prone position. Submaximal contraction will be assessed by instructing the participant to lift their arm while holding a handheld weight (e.g. based on subject’s body weight) while the evaluator examines the contralateral multifidus using the ultrasound [45, 46]. The thickness change in the multifidus muscle between sub-maximal (rest) and maximal (contracted) will be calculated using the following equation: %thickness change = (thickness_contracted_ − thickness_rest_)/thickness_rest_) × 100. This method of assessing multifidus using ultrasound is both reliable and valid as demonstrated by previous experiments [45, 47, 48].

##### Lumbar extensor muscle strength

Lumbar extensor muscle strength will be assessed with the use of the MedX lumbar extension machine. Participants’ hips, knees, and pelvis will be secured to the machine ensuring isolation of the lumbar extensor muscles with the axis of movement being fixed between vertebral levels L5-S1. This dynamometer assesses isometric lumbar extension muscular strength (torque) in a seated position and accommodates the dynamic resistance through a full 72° range of motion (ROM). Therefore, maximum lumbar extension torque will be assessed as maximum voluntary isometric contraction (MVIC) in lumbar extensor muscle strength in seven positions: 72°, 60°, 48°, 36°, 24°, 12° and 0° of flexion [41, 49]. Participants will be seated and positioned in the equipment; initial testing will be performed to verify any limitations in their ROM and adjustment for the counterweight [48]. Participants will first perform a slow controlled warm up for ~ 1 min, and then the maximum strength test will begin [41]. Verbal encouragement will be provided to encourage participants to generate maximum torque. The movement arm of the MedX machine is attached to a load cell that is interfaced with a computer, what will record and calculate torque measurements.

##### Disability

The Oswestry Disability Index (ODI) will be used to measure participants’ level of self-reported disability in relation to LBP. It is a 10-item scale in which each item is rated from 0 to 5, where 0 means that their pain does not influence that situation and a score of 5 indicates severe disability. The categories included in the questionnaire are pain, walking, lifting, sitting, standing, personal care, sleeping, travel, sex life, and social life. Scores are categorized as minimal, moderate, severe, crippled, or bed bound. The ODI has shown good reliability and validity, and therefore is considered to be the gold standard of measuring disability related to low back pain [50].

##### Health related quality of life

The 12-item Short Form Health Survey (SF-12) is the condensed form of the previous 36-item survey and will be used to assess participants’ health-related quality of life. The 12-item survey consists of 8 domains that assess both physical and mental components of health: 1) limitations in physical activities because of health problems, 2) limitations in social activities because of physical or emotional problems, 3) limitations in usual role activities because of physical health problems, 4) bodily pain, 5) general mental health (psychological distress and well-being), 6) limitations in usual role activities because of emotional problems, 7) vitality (energy and fatigue) and 8) general health perceptions. Scores from each of the 12 questions are combined to give an overall score between 0 and 100, with a score of 100 indicating the highest level of health. Given that this is a condensed version of a longer and established questionnaire, it has been extensively tested and shown to be both reliable and valid [51, 52].

##### Pain

The Visual Numerical pain rating scale (NPR) will be used to assess participants’ level of pain. The NRP is a self-reported rating system for pain intensity. Ratings range from 0 to 10 with 0 being no pain, 1–3 being mild pain, 4–7 being moderate pain, and 8–10 being extreme pain. This scale has excellent reliability and validity, and can be used detect statistical and clinically significant changes in perceived pain [53, 54].

### Possible effect modifiers

#### Catastrophizing: pain Catastrophizing scale (PCS)

The PCS is a 13-item questionnaire and will be used to assess participants’ level of catastrophizing. Each item is rated from 0 to 4 for a possible total of 52. The questionnaire focuses on three domains that have been used to describe catastrophizing: attentional focus on pain related thoughts (rumination), exaggeration of painful stimuli (magnification), and adopting a hopeless orientation with coping (helplessness). The higher the score, the higher the level of catastrophizing, with scores above 30 being clinically significant. This scale is both reliable and valid [55, 56].

#### Kinesiophobia: Tampa scale of Kinesiophobia (TSK)

The TSK will be used to measure participants’ fear of movement or reinjury in the presence of pain. The TSK-11 contains 11 phrases related to kinesiophobia, such as “I’m afraid I might injure myself if I exercise”, with each rating as a Likert scale from 1 to 4. The scores range between 11 and 44 with increasing scores showing increased levels of kinesiophobia. This tool has been shown to have high reliability and validity [57].

#### Depression: hospital anxiety and depression scale (HADS)

The HADS is a 14-item questionnaire and will be used to assess participants’ level of depression and anxiety. Seven items are related to depression while the other 7 relate to anxiety. Cognitive, behavioural, and emotional symptoms are covered in the questionnaire. Each item is rated from 0 to 3 with either depression or anxiety having scores between 0 and 21, with 21 being the highest level possible. Scores for either domain between 0 and 7 are classified as normal, 8 to 10 as borderline, and 11 to 21 as abnormal or elevated. The HADS was found to be both reliable and valid [58].

#### Sleep: insomnia severity index (ISI)

The ISI will be used to assess self-reported quality of sleep. It contains 7 questions than consider the ability to fall asleep, the ability to stay asleep, and effects on daily life. Each question is rated with a Likert-scale from 0 to 4, with lower ratings indicating a higher quality of sleep. Scores between 0 and 7 indicating no clinically significant insomnia, 8 to 14 indicating subthreshold insomnia, 15 to 21 indicating moderate insomnia, and 22 to 28 indicating severe insomnia. Fourteen has been commonly used as the cut-off score to detect primary insomnia. The reliability and validity of this tool has been demonstrated [59].

#### Physical activity: international physical activity questionnaire (IPAQ)

The IPAQ will be used to assess participants’ level of physical activity. The IPAQ is a self-reported log of physical activity (METs based on intensity) in minutes per week over a span of 7 days. The level of physical activity is rated either vigorous (8 MET), moderate (4 MET), walking (3.3 MET) and sitting/rest (1 MET) and must be assigned to the right category. The number of minutes per category is then added up and results are classified as high, moderate, or low physical activity based on the total MET minutes. This measure has been deemed both reliable and valid [60].

### Data monitoring

#### Adverse events

The occurrence of adverse events (e.g., muscle soreness and temporary increase in LBP) will be monitored by the therapists during the intervention and at the end of the intervention using open ended questions.

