### Blinding

Only the assessor will be blinded, as blinding of therapists and participants is generally not possible in exercise intervention trials [29].

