### Procedure

All research activities will take place at the PERFORM Centre, Concordia University. This centre houses 8000m^2^ of laboratories, assessment suites, and lifestyle intervention space, all designed specifically to foster interdisciplinary environment devoted to health prevention research. The infrastructure has all the necessary research platforms (e.g., Imaging Suite, Conditioning floor and Functional Assessment suite) for the conduction of the proposed RCT.

Eligible participants will be randomized between the GE (*n* = 25) and MC + ILEX (n = 25) groups. The participants of the two groups will undergo a 12-week intervention programme with two individually supervised exercise sessions per week of approximately 45 min. The treatment will be provided by a certified athletic therapist (MC + ILEX) with 2 y of clinical experience or graduate exercise science master’s student (GE). Participants in both groups will be advised to complete a home exercise programme during the intervention and after discharge. During the intervention period, participants will be asked to refrain from receiving other types of treatment (e.g., chiropractor, osteopath, massage) and medication, although this will not hinder participation. Participants will be asked to report any co-interventions.

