### Sample size calculation

Sample size calculation was determined by using the effect size (e.g., significant pre-post difference in multifidus muscle CSA measurements following a motor-control exercise intervention) from a previous study^62^ (e.g., previously reported effect size (95% CI) for each spinal level; L2 = 0.87(0.20,1.54); L3 = 0.90 (0.19,1.62); L4 = 1.00(0.32, 1.67), and L5 = 0.81(0.10,1.53)) [62]. The mean effect size (over the 4 different spinal levels) was calculated and used for sample size estimation. Pre-post results were considered as independent (independent from two groups) to concur with the present study statistical analysis (between-group factor). Therefore, sample size estimation was calculated with the G*power software (mean difference, independent t-test) on the basis of a mean effect size d = 0.90, 80% power and a significance level of alpha 0.05, and allowing for a 10% lost to follow-up and 10% treatment non-adherence.

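### Adverse events are elicited with open-ended questions by unblinded treatment providers whose type differs by arm, so any between-arm description of harms is open to differential ascertainment

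*Protocol article*

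**What the plan says.** Under Data monitoring, the Adverse events section is one sentence. It names the collector: "The occurrence of adverse events (e.g., muscle soreness and temporary increase in LBP) will be monitored by the therapists". It also gives the timing and method: "during the intervention and at the end of the intervention using open ended questions".

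Three other sections bear on it:

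- **Procedure** names the provider for each arm, a "certified athletic therapist (MC + ILEX) with 2 y of clinical experience or graduate exercise science master’s student (GE"). It also sets the contact schedule, a "12-week intervention programme with two individually supervised exercise sessions per week of approximately 45 min".
- **Blinding** states: "Only the assessor will be blinded, as blinding of therapists and participants is generally not possible in exercise intervention trials".
- **Data collection** has self-reported questionnaires at baseline, 6 and 12 weeks and again at a 24-week follow-up, completed on paper or through a LORIS link. Adverse events are not among the measures described for them.

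**The concern.** When harms are compared between arms, the question and the person judging the answer should be the same in both. Here the method the article describes ties the type of observer to the treatment. Each provider, on the natural reading, records the harms of the programme that he or she delivers, knows the allocation, and has a different professional background from the provider in the other arm.

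The kinds of event named make this matter more. Muscle soreness and a temporary increase in low back pain are matters of degree, and every participant enters with chronic low back pain and moderate or severe disability. With open-ended questions and no threshold in the article, it falls to the provider to decide what is worth probing and writing down. No later analysis can separate a true difference in harm from a difference in asking or recording, because observer type and arm coincide.

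At stake is the harm side of the trial's message. A statement that one programme caused more soreness or flares than the other, or that the two were equally well tolerated, would be hard to defend.

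**Working it through.** The plan gives no adverse-event rate or comparison, so there is no figure of its own to reproduce. The check has three steps.

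**1. Who asks, and does that differ by arm?**

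| Feature | MC + ILEX | GE | Source |
|---|---|---|---|
| Treatment provider | Certified athletic therapist, 2 years' experience | Exercise science master's student | Procedure |
| Provider blinded? | No | No | Blinding |
| Adverse-event collector | The therapists | The therapists | Adverse events |
| Form of question | Open-ended | Open-ended | Adverse events |

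That the therapists in the last two rows are the providers in the first row is the natural reading, but it is not stated outright. On that reading the observer type differs completely between arms. By contrast, the Adherence section, also under Data monitoring, uses a fixed five-level item for home exercise.

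**2. How large could the distortion be?**

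Inputs from the article: 25 participants per arm (Procedure). Assumed inputs, not in the article: the same true event proportion p in both arms (20%, 40% or 60%), and capture probabilities s1 and s2 for the two providers.

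- Expected recorded events in an arm = 25 × p × s
- Spurious risk difference = p × (s1 − s2)

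| p | s1, s2 | Expected recorded events | Spurious risk difference |
|---|---|---|---|
| 0.20 | 0.90, 0.90 | 4.5 vs 4.5 | 0 |
| 0.20 | 0.90, 0.70 | 4.5 vs 3.5 | 0.20 × 0.20 = 4 points |
| 0.20 | 0.90, 0.50 | 4.5 vs 2.5 | 0.20 × 0.40 = 8 points |
| 0.40 | 0.90, 0.90 | 9.0 vs 9.0 | 0 |
| 0.40 | 0.90, 0.70 | 9.0 vs 7.0 | 0.40 × 0.20 = 8 points |
| 0.40 | 0.90, 0.50 | 9.0 vs 5.0 | 0.40 × 0.40 = 16 points |
| 0.60 | 0.90, 0.90 | 13.5 vs 13.5 | 0 |
| 0.60 | 0.90, 0.70 | 13.5 vs 10.5 | 0.60 × 0.20 = 12 points |
| 0.60 | 0.90, 0.50 | 13.5 vs 7.5 | 0.60 × 0.40 = 24 points |

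Nothing in the article indicates which provider would record less, so the sign is unknown.

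**3. Are participants who stop attending missed?**

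The article does not say. The only therapist contact it describes is the supervised sessions, but the end-of-intervention questioning is not tied to a session and could include people who have stopped. The Co-interventions section says that medication information is gathered on all participants; the Adverse events section has no equivalent statement. The sample size section is no help in putting a number on this. Its allowances ("allowing for a 10% lost to follow-up and 10% treatment non-adherence") amount to 0.10 × 50 = 5 and 0.10 × 50 = 5 participants, but they were set for power, and a non-adherent participant may still attend and be asked.

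**The case against.** The strongest case on the other side has four parts.

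- **Harms are not a planned comparison.** Adverse events are not among the aims, the listed outcomes or the measures to be analysed. They sit with adherence and co-interventions as monitoring. This is correct and limits the point: no planned inference and no sample size depends on it. It does not remove the point, because a trial that asks whether one programme is superior to the other will be expected to describe harms by arm.
- **The article is condensed.** A standard form, definitions and follow-up of withdrawals may stand in the full protocol. This is fair, and their absence is not held against the plan. What is criticised is the method that the article does state: who asks, and by what kind of question. For the same reason, the therapists can be called only the one source the article names.
- **Worsening pain is measured anyway.** The pain scale and the disability index are self-completed, identical in both arms and available remotely. That does cover sustained worsening independently of the therapist, and the 24 supervised sessions give frequent contact. Brief flares between questionnaires, and soreness, still depend on the provider.
- **Closed items can miss the unexpected.** True, and it is the reason to add a closed item and not to replace the open question.

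A reader might go further and infer that harms are sought only at attended sessions and that dropouts are left out, perhaps up to 10 of 50. The article says neither, and the 10 would come from adding power allowances that do not describe adverse-event collection. Nor can one assumed pair of capture rates stand as an estimate of the bias.

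**Conclusion.** The point holds in a limited form. As described, harms are ascertained by unblinded providers, without a standardised question, and the type of provider differs by arm. Any between-arm description of adverse events is therefore open to differential ascertainment that cannot be corrected afterwards.

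The 4- to 24-point range illustrates what unequal capture could do; it is not a prediction. It rests on the assumed event proportions and capture rates, and on reading the therapists as each arm's own providers. Loss of non-attenders is a risk that the text leaves open, not a feature that it states, and its extent cannot be derived. The consequence is confined to the harm data; the primary analysis of multifidus morphology stands as planned. The change is worth making because it is cheap.

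**What to change.** Keep the therapists' open-ended logging for immediate safety and for events that nobody anticipated. Add a short adverse-event item, worded identically for both arms, to the self-completed 6- and 12-week questionnaires, and name it as the source for any between-arm comparison of harms. Send it on paper or by LORIS link to every randomised participant, including those who have stopped attending, and say so in the Adverse events section. Self-completion means that the blinded assessor need not ask about the exercises, which protects that blind.

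The cost is a few lines on existing forms and a change of protocol wording, with no extra staff or visits. Two downsides remain. A direct question will bring in more minor events. Participants also know which exercises they are doing, so the source is still unblinded, although the question no longer differs by arm. Some participants who are truly lost will not answer a link either; the change reduces that gap but does not close it.

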**Methods:**

A total of 50 participants with chronic non-specific LBP and moderate to severe disability, aged between 18 and 60, will be recruited from the local orthopaedic clinics and university community. Participants will be randomised (1:1) to either the MC + ILEX or GE group. Participants will undergo 24 individually supervised exercise sessions over a 12-week period. The primary outcome will be multifidus morphology (atrophy) and composition (fatty infiltration). Secondary outcomes will be muscle function (e.g., % thickness change during contraction), morphology, lumbar extension strength, pain intensity and disability. Potential treatment effect modifiers including maladaptive cognitions (fear of movement, catastrophizing), anxiety, depression, physical activity, and sleep quality will also be assessed. All measurements will be obtained at baseline, 6-week and 12-week; self-reported outcomes will also be collected at 24-week. Between-subjects repeated measure analysis of variance will be used to examine the changes in paraspinal muscle morphology over the different time points. Linear mixed models will be used to assess whether baseline scores can modify the response to the exercise therapy treatment.

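### Adverse event collection stops when the 12-week intervention ends, although home exercise is advised after discharge and participants are contacted again for self-reported outcomes

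*Protocol article*

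**What the plan says.** All references are to the protocol article.

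- **Adverse events** (under Data monitoring): events "will be monitored by the therapists during the intervention and at the end of the intervention using open ended questions". The section's examples are sore muscles and a short-lived worsening of back pain.
- **Procedure**: participants "will undergo a 12-week intervention programme with two individually supervised exercise sessions per week of approximately 45 min". The same section says: "Participants in both groups will be advised to complete a home exercise programme during the intervention and after discharge".
- **Data collection**: "All outcomes (as described further) will be obtained at baseline, 6-week and 12-week for both intervention groups". It then adds: "The self-reported outcomes will also be assessed 24-week post-intervention".
- **Abstract, Methods**: "self-reported outcomes will also be collected at 24-week".
- **Co-interventions**: other treatments are to be reported for the intervention period only.

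**The concern.** The adverse events sentence fixes who collects, how and when. It can therefore be compared with the exposure and follow-up described elsewhere in the article, and the three do not end together. Advised exercise and self-reported outcomes both continue past the point at which anyone asks about harms. The later period is also the one without supervised sessions.

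At stake is how complete the harms report is. If the trial reports pain and disability to its last contact but adverse events only to week 12, a reader weighing one programme against the other sees benefit and harm over different periods. A flare that came and went after discharge would leave no trace. A lasting one would show only as a worse pain or disability score.

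**Working it through.** No power or variance calculation bears on this point. The check compares the stated windows.

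**Inputs**

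1. Supervised intervention: 12 weeks at two sessions per week (Procedure). 12 × 2 = 24 sessions, which agrees with the Abstract.
2. Adverse event window: the intervention and its end, so weeks 0 to 12 (Adverse events).
3. Home exercise: advised during the intervention and after discharge, with no end date (Procedure).
4. Last self-report contact: week 24 (Abstract), or 24 weeks after the intervention (Data collection, read literally), which is 12 + 24 = week 36.
5. Participants: 50 (Abstract).

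**Windows side by side**

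| Item | Ends at |
|---|---|
| Adverse event collection | week 12 |
| MRI (primary), ultrasound, strength | week 12 |
| Self-reported outcomes, including pain and disability | week 24 or week 36 |
| Advised home exercise | no end stated |

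**Length of the uncovered period**, from the end of the adverse event window to the last contact:

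- Last contact at week 24: 24 − 12 = 12 weeks per participant. With all 50 retained, 50 × 12 = 600 person-weeks.
- Last contact at week 36: 36 − 12 = 24 weeks per participant. With all 50 retained, 50 × 24 = 1200 person-weeks.

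These are lengths of calendar time. The article gives no event rate and no content or dose for the home programme, so they cannot be turned into a number of missed events.

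**Does anything else in the article fill the gap?**

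- *Last pain and disability scores.* They would show a worsening still present at that contact, though as an outcome and not as an adverse event. The section's own examples are transient, so they can start and resolve between week 12 and the last questionnaire without moving the score.
- *Co-interventions.* The question covers the intervention period, so care sought for a later flare is not captured there.
- *Adherence.* This section intends to measure home exercise after discharge, which shows that the trial treats that phase as worth recording. It asks nothing about harms.

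**The case against.** The strongest case against is that active enquiry about harms during the treatment period is a defensible choice in a low-risk exercise trial with an active comparator. The sentence also stands in a condensed article, and a fuller protocol may say more. The gap applies to both arms and changes neither the primary analysis nor the sample size. Much of this stands, and it keeps the point small. It does not remove it: the article states a window, and nothing shown extends it. A gap shared by both arms still leaves harms incomplete in both.

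A reader might infer several stronger things that the document does not support.

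- *That harms from the baseline maximal strength test are lost.* That test does precede training: the "one repetition maximum (1RM) will have been recorded during the baseline testing", and "maximum lumbar extension torque will be assessed as maximum voluntary isometric contraction (MVIC". But it is an assessment made in both arms, not part of an assigned treatment, and soreness after it could surface in the therapists' open-ended questions at the first sessions. The week-6 test lies inside the window and the week-12 test at its end.
- *That the later home exercise is prescribed and differs by arm.* The text says only that it is advised in both groups and does not describe its content.
- *That later harms go entirely unrecorded.* A lasting rise in pain or disability would appear in the last scores. What is missing is a stated collection point for adverse events as such.
- *That all benefit is followed for longer than harm.* Only the self-reported outcomes are. Imaging and strength stop at week 12.
- *That coverage of 12 of 24 or 12 of 36 weeks measures missed risk.* All 24 supervised sessions, with all the supervised loaded training, fall inside the window, so share of time is not share of risk.

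**Conclusion.** The point holds as a limited shortfall in harms ascertainment. As written, the post-discharge period of 12 or 24 weeks per participant, depending on which statement of the last contact is right, has no stated collection of adverse events. Harms are thus reported over a shorter period than self-reported pain and disability. The primary MRI comparison and the planned 50 participants are unaffected.

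The conclusion rests on two assumptions: that the adverse events sentence is the whole rule, and that the later questionnaire contains no adverse event item. If the full protocol already collects adverse events at the last contact, only the article's wording needs correcting.

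**What to change.** Extend the window in the Adverse events section to the last self-report contact. Add one item to the questionnaire already planned for that contact, asking about new or worsened symptoms, injury, or care sought since the end of the intervention.

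Report these events by arm, separately from those found during the therapist-monitored period. One set comes from repeated enquiry by therapists and the other from a single recall question, so the two should not be pooled as if ascertained alike.

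Reconcile the Abstract and Data collection on the timing of the last contact, so that the end of the window is defined. If the sponsor prefers not to extend collection, the article should state that harms after the intervention are not covered.

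The cost is one short item on an existing paper or online form and a change of wording, with no extra visit. The downside is a few more minor events to log, with some recall error.
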